## Abstract

**Background:**

Multiple sclerosis (MS) is a degenerative disease of the central nervous system (CNS) that disrupts walking function and results in other debilitating symptoms. This study compares the effects of ‘task-oriented exercise’ against ‘generalized resistance and aerobic exercise’ and a ‘stretching control’ on walking and CNS function in people with MS (PwMS). We hypothesize that task-oriented exercise will enhance walking speed and related neural changes to a greater extent than other exercise approaches.

**Methods:**

This study is a single-blinded, three-arm randomized controlled trial conducted in Saskatchewan, Canada. Eligible participants are those older than 18 years of age with a diagnosis of MS and an expanded Patient-Determined Disease Steps (PDDS) score between 3 (‘gait disability’) and 6 (‘bilateral support’). Exercise interventions are delivered for 12 weeks (3 × 60-min per week) in-person under the supervision of a qualified exercise professional. Interventions differ in exercise approach, such that task-oriented exercise involves weight-bearing, walking-specific activities, while generalized resistance and aerobic exercise uses seated machine-based resistance training of major upper and lower body muscle groups and recumbent cycling, and the stretching control exercise involves seated flexibility and relaxation activities. Participants are allocated to interventions using blocked randomization that stratifies by PDDS (mild: 3–4; moderate: 5–6). Assessments are conducted at baseline, post-intervention, and at a six-week retention time point. The primary and secondary outcome measures are the Timed 25-Foot Walk Test and corticospinal excitability for the tibialis anterior muscles determined using transcranial magnetic stimulation (TMS), respectively. Tertiary outcomes include assessments of balance, additional TMS measures, blood biomarkers of neural health and inflammation, and measures of cardiorespiratory and musculoskeletal fitness.

**Discussion:**

A paradigm shift in MS healthcare towards the use of “exercise as medicine” was recently proposed to improve outcomes and alleviate the economic burden of MS. Findings will support this shift by informing the development of specialized exercise programming that targets walking and changes in corticospinal excitability in PwMS.

**Trial registration:**

ClinicalTrials.gov, NCT05496881, Registered August 11, 2022. https://classic.clinicaltrials.gov/ct2/show/NCT05496881. Protocol amendment number: 01; Issue date: August 1, 2023; Primary reason for amendment: Expand eligibility to include people with all forms of MS rather than progressive forms of MS only.

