#### Blood marker measures

Systemic blood markers to be measured are serum TNF-α [35], BDNF [34], and NF-L [37, 38]. Blood samples are collected by a licensed phlebotomist at an off-campus location by venipuncture from the antecubital fossa to a vacutainer tube with no additive. The samples are allowed to clot and then centrifuged at 2,000 g for 30 min at 4 °C. Serum is aliquoted, transported to campus on ice, and stored at -80 °C within two hours of collection. Concentrations of all analytes will be measured using assays with appropriate sensitivity and reliability. Given low concentrations of NF-L, ultrasensitive assays will be considered for analysis in addition to more standard enzyme-linked immunosorbent assays. Assays will be run by a study team member in a preliminary analysis once a third of the projected sample has completed the study. Additional samples will be run in a single, batched analysis following completion of all data collection. Further blood markers linked to MS disease progression and exercise (e.g., interleukin-6) may be added to the analysis protocol if sample volume permits.

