#### Statistical analysis and sample size calculation

Baseline data collection will include both demographic and MS-related information (Table 3). The primary statistical analysis will compare T25-FWT performance at the post-intervention time point between the three study arms using ANCOVA (analysis of covariance) with a between-groups factor (task-oriented, generalized resistance and aerobic exercise, stretching control) and adjusting for baseline T25-FWT performance [28]. Planned pairwise comparisons will directly test differences between each study arm. Comparison of the secondary outcome and all other outcome measures at the post-intervention time point across study arms will follow the primary analysis methods (i.e., ANCOVA adjusting for relevant baseline measure). Exploratory analysis of change in outcome measures across all time points and between study arms will use a linear mixed effects model with Time point, Study arm, and Baseline T25-FWT performance as fixed factors. Participant will be a random factor. The models will account for dependencies/correlations resulting from repeated measurements. Final exploratory analyses will re-run all statistical tests with data disaggregated by sex [70–72]. For all statistical tests, the alpha will be 0.05. Point and 95% confidence interval estimates for study arm differences will be determined. Participants will be analyzed in the study arm to which they were randomized (i.e., intention-to-treat principle). Multiple imputation will be used to minimize biased estimates from missing data with the analysis based on a missing at random assumption [73]. We will conduct an interim analysis when 50% of the sample has completed study procedures. This interim analysis will allow dissemination (i.e., conference presentations) of preliminary findings. There is no stopping rule for the trial because no serious adverse events from the intervention are anticipated.

**Table 3 Tab3:** Baseline data collection variables

Variables
Age (years)
Sex
Gender (optional)
Height
Weight
BMI
Type of MS
Year of MS onset (e.g., first symptom)
Year of MS diagnosis (by a neurologist)
Most recent relapse (month/year)
Patient Determined Disease Steps
Walking aid or assistive devices
More affected side (upper and lower body)
Medications (including disease-modifying therapy)
29-Item Multiple Sclerosis Impact Scale
Clinical MRI availability
Other health conditions
Employment/Work status
Typical Day
Fall history past 7 days

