Several challenges and limitations need to be considered. The nature of the study prohibits indisputable blinding of participants and intervention instructors. Strategic scheduling of interventions and providing instructors only with necessary information mitigate potential confounds. The activities of participants outside of intervention scheduling and between intervention end and the retention time point also cannot be controlled, but information on extracurricular physical activity is collected in the study exit survey for consideration in results interpretation. Another consideration is that we plan to recruit participants with all types of MS, which present with different disease courses and potentially different neurobiology [4]; however, this approach is consistent with other related research [21, 22] and may improve generalizability of results. Given prior research suggesting limited retention of effects of exercise interventions on motor function [31], the long-term benefits of this work for PwMS may be questioned. It is plausible that the targeted nature of the task-oriented training employed in the current research will result in more persistent benefits than prior work. Nevertheless, it is likely that PwMS require more than a single 12-week intervention to maximize and retain functional improvements in the long-term. Instead, this work should be considered a critical step towards development of optimal intervention strategies that will require ongoing or cyclic delivery for the maximum benefit of PwMS. Finally, the limitations of our physiological outcome measures must also be acknowledged. TMS is an inherently variable technique that probes specific neural mechanisms [42] which overlap only partially with mechanisms of neuroplasticity that may support functional gains induced by task-oriented exercise [81]. Likewise, systemic blood markers may not precisely reflect changes occurring in the CNS [38].

Recent work highlighted the lack of evidence for exercise effects on functional outcomes and CNS change in PwMS [46]. The current study is guided by the mechanistic hypothesis that task-oriented exercise, relative to other exercise approaches, may maximize functional gains in PwMS by preferentially engaging experience- or learning-dependent changes in corticospinal excitability. Findings have potential to improve understanding of the best approach to improve walking function for PwMS.

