### Trial status

Participant enrolment began in May 2022 and recruitment is ~ 30% complete. Note that the clinical trials registration with our planned recruitment start date was submitted prior to recruiting any participants. However, one participant was recruited but no participants started the intervention before the trial was officially registered (August 11, 2022). The trial is expected to be complete by January 2025.

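### After eligibility was widened mid-recruitment from progressive to all forms of MS, the stated analyses use neither MS type nor serum assay run; this costs some precision and clouds marker levels but does not bias the arm contrasts

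*Protocol article*

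**What the plan says.** The Trial registration section gives "Protocol amendment number: 01; Issue date: August 1, 2023", with the reason "Expand eligibility to include people with all forms of MS rather than progressive forms of MS only". Trial status reports "Participant enrolment began in May 2022 and recruitment is ~ 30% complete", without saying on what date that held.

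Study participants and Table 3 list MS type among the baseline variables. Study arm allocation stratifies on PDDS alone (3–4 versus 5–6) and uses small blocks of unstated size. The Background says walking impairment tends to be greater in progressive forms. The Discussion says the types are ones "which present with different disease courses and potentially different neurobiology", and defends the mix as consistent with related research and as a possible gain in generalizability.

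Statistical analysis and sample size calculation gives a model for every outcome:
- The primary ANCOVA compares arms "adjusting for baseline T25-FWT performance".
- All other outcomes use the same ANCOVA with their own baseline value.
- The exploratory mixed model has time point, arm and baseline T25-FWT.
- The only disaggregation is by sex.

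MS type appears in none of these.

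For serum TNF-α, BDNF and NF-L, Blood marker measures says: "Assays will be run by a study team member in a preliminary analysis once a third of the projected sample has completed the study". It continues: "Additional samples will be run in a single, batched analysis following completion of all data collection". No term for assay run is described.

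**The concern.** The target population changed while the trial was recruiting, and the stated analysis does not respond. The article itself treats MS type as related to walking and possibly to neurobiology. A baseline variable that it considers prognostic is therefore collected and then left in the residual. The article claims generalizability across types, but no planned output shows the arm effect by type.

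The serum plan adds a second, smaller problem. The first run will hold mostly or wholly people enrolled under the progressive-only criteria, and the later batch a mixed group. A shift in level between runs would then be hard to separate from a difference between disease types when pooled marker values are described or interpreted.

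At stake are precision and interpretability. The blood markers are tertiary outcomes, so the assay part does not touch the primary T25-FWT or the secondary active motor threshold.

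**Working it through.** **1. The plan's sample size.** Inputs from Statistical analysis and sample size calculation: d = 0.95, two-sided alpha 0.05, power 85%, equal allocation. A two-sample t-test (noncentral t) needs 20.90, so 21 per arm and 63 in total, as stated. Power at 21 per arm is 85.2%. (The normal approximation gives 20 per arm.)

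**2. Timing.** May 2022 to 1 August 2023 is about 15 months. The reported recruitment is 0.30 × 63 = 18.9, about 19 people. The early assay run is triggered at 63/3 = 21 completers, which leaves 63 − 21 = 42 for the later batch.

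**3. Precision of the primary comparison.** The documents give no share of variance for MS type, so it is assumed. Let type account for a share r of the residual variance left after baseline, on top of the variance behind d = 0.95. The standardized effect becomes 0.95 × √(1 − r).

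| Assumed r | Effect | Power at 21 per arm | Per arm for 85% |
|---|---|---|---|
| 0 | 0.950 | 85.2% | 21 |
| 2% | 0.940 | 84.5% | 22 |
| 5% | 0.926 | 83.3% | 22 |
| 10% | 0.901 | 81.3% | 24 |

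An outer case of 20% gives 76.6%. If the planning variance already contained the type effect, there is no loss. Adjusting for type would then raise power to 85.9%, 86.9% or 88.6% at 2%, 5% or 10%.

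**4. Chance imbalance in MS type between two arms.** Assume the first third is all progressive and evenly split, 7 per arm. Imbalance can then arise only among the later 14 per arm. With p the relapsing share among later enrolees, the 95% range is (2/3) × 1.96 × √(2p(1 − p)/14). Overall relapsing shares of 30%, 50% and 65% (assumed) require p = 45%, 75% and 97.5%:
- p = 0.45: ±25 percentage points
- p = 0.75: ±21 points
- p = 0.975: ±8 points

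**5. Overlap of assay run and MS type.** Let P be the overall progressive share, p1 the share in the first 21 and q the share in the later 42. Then P = (21·p1 + 42·q)/63 and phi = (1/3)(p1 − P)/√[(1/3)(2/3)P(1 − P)]. For p1 = 1 and q = 0.5, P = 0.667 and phi = 0.111/0.222 = 0.50.
- p1 = 1, with q = 20%, 35%, 50%, 65%, 80%: phi = 0.76, 0.62, 0.50, 0.39, 0.28.
- p1 = 0.9, over the same q: phi falls from 0.67 to 0.13.

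The overlap is partial as long as people with progressive MS keep enrolling.

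**6. Effect on arm contrasts for a marker.** A 5,000-run simulation used 63 participants, two strata and blocks of 3 or 6. All of the first 21 and half of the later 42 were progressive. A run shift of 1 unit acted on both baseline and post values, and a type effect of 0.5 unit acted on the post value. Mean bias in the arm difference was −0.004 (blocks of 3) and −0.003 (blocks of 6), zero within simulation error. The standard error was 0.278 without run and type terms and about 0.267 with them: 0.278/0.267 = 1.04, a cost of about 4%.

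**The case against.** The strongest reply is that no planned comparison is harmed. Every planned contrast is between randomized arms, small blocks keep the arms close to equal over calendar time, and no contrast between MS types is planned for any marker. Chance imbalance is already reflected in the standard error. Baseline adjustment and PDDS stratification absorb much of the impairment difference that goes with type. All of this stands, and it limits the point to precision and interpretation.

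The documents do not support several stronger readings that a reader might infer:
- **That the amendment came at 30% recruitment.** The 30% is an undated status at the time of writing. No figure is given for 1 August 2023.
- **That the assay split coincides with the eligibility change.** The first run starts "once a third of the projected sample has completed the study". Completion means week 18, so the run may include some people with relapsing MS.
- **That the NF-L platform changes between runs.** The text only says ultrasensitive assays will be considered alongside standard ones.
- **That type imbalance could reach about ±28 to ±30 points.** That range, 1.96 × √(2p(1 − p)/21) for p between 0.30 and 0.65, treats all 21 per arm as one mixed population. This conflicts with an early third that is largely progressive.

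It can also be said that the Discussion acknowledges the heterogeneity, and that covariates and run terms belong in an analysis plan not shown here. Acknowledgement is not handling. The article also does more than stay silent: it states a model for each outcome, and it fixes a two-stage assay plan. One point stays open. The text does not say the early run is confined to completers' samples. If it is not, some participants' baseline and later samples would fall in different runs, and baseline adjustment would no longer absorb a run shift for them.

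**Conclusion.** The point holds as one of precision and interpretability. The arm contrasts are not biased, and the sample size of 63 reproduces.

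For the primary outcome, the loss is from 85.2% power to between 84.5% and 81.3%. This assumes that MS type adds 2% to 10% of residual variance, a share the documents do not give. For the blood markers, ignoring run and type costs about 4% in standard error in the one scenario simulated. Pooled marker levels are harder to interpret, with a run–type correlation between 0.28 and 0.76 if the first run is wholly progressive, and lower otherwise. The article's generalizability argument is left without any planned display of the arm effect by MS type. The remedy is cheap and recruitment was reported as only about 30% complete, so the change is worth making.

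**What to change.** 1. Prespecify MS type (progressive versus relapsing), already collected, as a covariate in the ANCOVAs or as a sensitivity analysis. Pre/post-amendment period is an acceptable alternative. Report arm effects by MS type with confidence intervals, labelled descriptive and exploratory, because 21 per arm will give imprecise estimates.
2. For TNF-α, BDNF and NF-L, hold all serum at −80 °C and assay it in one run on one platform after the last participant, keeping each participant's samples together. If the early run is kept, include assay run as a covariate in the marker models.

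The cost is one or two degrees of freedom and a few sentences of text. If the early run is dropped, biomarker results also come later.

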**Supplementary Information:**

The online version contains supplementary material available at 10.1186/s13102-023-00790-5.

## Background

Multiple sclerosis (MS) is a chronic, progressive neurological condition currently without a cure that affects over 90,000 Canadians and more than 2.8 million persons worldwide [1–3]. The disease is characterized by destruction of the myelin sheath, a fatty layer around neurons critical for transmission of neural signals [4]. Typically, MS is diagnosed between the ages of 20 and 49 years [5]. In relapsing-remitting MS, the most common form, myelin is destroyed unpredictably in ‘relapse’ periods that are followed by periods of remission. However, approximately 65% of people diagnosed with relapsing-remitting MS transition to secondary progressive MS within 25 years and experience an ongoing, progressive destruction of myelin and further neurodegeneration [4]. Also, 10–20% of people with MS (PwMS) experience the primary progressive form, which is usually diagnosed after the age of 40 without any early relapses or remissions [4]. Crucially, as the myelin sheath deteriorates and further neurodegeneration occurs, motor, sensory, and cognitive functions are lost [6].

Walking is one of the most disrupted and valued motor functions across all types of MS, although impairments tend to be greater in progressive forms due to marked weakness of the lower extremities [7–9]. Disease-modifying drugs are the primary treatment approach for PwMS [10], but the impact of these drugs on walking function is limited. For example, only one pharmaceutical has been shown to improve walking speed among PwMS [11]. In this work, nearly one third of PwMS treated with dalfampridine improved their walking speed by approximately 25% (95% confidence interval, 21.0–28.4%) [11].

Exercise is established as safe, feasible, and beneficial for people with all types of MS, including those with high levels of impairment [12–16]. Established physical activity guidelines for PwMS indicate that resistance training of major muscle groups and 30 min of moderate-intensity aerobic activity at least two days per week can improve muscular strength and aerobic capacity [17–19]. Participation in physical activity, such as exercise training, has increasingly been recommended for PwMS to manage symptoms, promote wellness, boost participation in activities of daily living, and optimize quality of life [20]. Nevertheless, there remains limited understanding of what the best approach to exercise is for PwMS in terms of achieving functional outcomes. While meta-analyses have concluded that exercise among PwMS is associated with statistically significant improvements in walking speed, the magnitude of such improvements vary from large and clinically important to trivial across studies [21–24]. Interpretation of findings from exercise research in PwMS is limited by the use of generic or ill-defined interventions, few comparisons between exercise approaches, minimal consideration of impairment level, and limited use of functional outcomes [21, 22]. As a result, the “key ingredients” required for exercise to improve functional outcomes, such as walking speed, for PwMS remain largely undocumented.

Exercise training for people with sudden-onset neurological conditions (e.g., stroke) often employs a task-oriented approach, which refers to repetitive, goal-directed task practice that targets specific deficits in motor function [25–27]. Like other approaches to exercise, task-oriented exercise provides a stimulus to improve fitness, but its emphasis is on the re-learning of skills that were lost due to neurological damage and/or associated disuse. Although initial work suggests that task-oriented exercise may improve walking function in PwMS [14, 28, 29], it is not known if task-oriented exercise is superior to other exercise approaches. Evidence supporting the use of task-oriented exercise in PwMS was obtained from studies that unsystematically included task-oriented elements within other exercise approaches [21, 22], used a pre-post design with no control intervention [30, 31], compared the task-oriented approach to a non-exercise control intervention only [14, 32], or did not evaluate follow-up effects [30, 31]. Moreover, considering the degenerative nature of the disease, it is unclear if the emphasis on re-learning skills in task-oriented exercise is important for PwMS to optimize function or if more generalized approaches to exercise provide similar outcomes.

Central nervous system (CNS) changes following exercise have been reported in a small body of work in PwMS. Most of this work considers global changes in CNS health, reflected by changes in systemic blood markers of neuroinflammation and neuroprotection [33, 34]. For example, MS is associated with high systemic levels of the pro-inflammatory cytokine tumor necrosis factor-alpha (TNF-α) [35], which may be decreased by participation in regular exercise [36]. Neurotrophic factors, a family of biomolecules involved in neuroprotection, are also commonly examined (e.g., brain-derived neurotrophic factor, BDNF), and evidence suggests that BDNF may increase with exercise in PwMS [34]. Neurofilament light chain (NF-L) [37, 38], a cytoskeletal protein that reflects neuronal damage when detected in systemic blood, may better characterize the progression of the disease [39, 40], with evidence suggesting that it is decreased with regular aerobic exercise [41]. Nevertheless, conflicting findings and variable exercise interventions (i.e., type, intensity, duration) have limited the conclusions that can be drawn about exercise effects on blood markers of CNS health in PwMS [16, 33, 34]. Importantly, the neurophysiological effects of task-oriented exercise may extend beyond global improvements in CNS health to also include more specific changes in neural pathways involved in the ‘re-learning’ of motor skills. Such changes in the CNS can be measured with transcranial magnetic stimulation (TMS) [42]. While TMS-based measurements have been explored in PwMS for their utility as markers of disease burden [43], they can also be used to examine specific experience- or learning-dependent changes in the excitability of neural pathways that may be targeted by skill-based activities used in task-oriented exercise.

The overall goal of this work is to accelerate the development of improved exercise approaches for PwMS by characterizing the distinct functional effects and mechanistic underpinnings of task-oriented exercise for walking. The objective of the study is to compare the effect of task-oriented exercise against generalized resistance and aerobic exercise and a stretching control intervention on walking and CNS function in PwMS. Our primary hypothesis is that task-oriented exercise focused on walking will result in greater improvements in walking speed in PwMS than the alternate exercise interventions. We postulate that these task-oriented effects on walking speed will be accompanied by increases in corticospinal excitability for the ankle dorsiflexors that are not elicited by the other exercise approaches. Finally, we expect that exercise effects on musculoskeletal and aerobic fitness and global markers of CNS health will be similar across task-oriented and generalized resistance and aerobic exercise approaches, but greater than effects elicited by the stretching control intervention.

